### Sample size and power calculation

A previous exercise intervention study provided VO_2peak_ data from a CFS sedentary, age-matched cohort (16.2±1.3 yr) [18]. This data has been used to compute statistical power *a priori* using the non-commercial statistical power analysis program G*Power. The control group is expected to experience no change in the aerobic capacity after 12-weeks while the intervention groups are expected to increase this measure following the exercise interventions. Setting an alpha level of 0.05, approximately 75 participants (25 per group) will provide 82% power to detect a statistically significant difference between groups. Recruitment will be inflated to 90 participants to enable a 20% participant attrition rate.

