Strategies to manage CFS include pharmacology, physical activity where appropriate (for example graded exercise (GE) and pacing), and psychological approaches such as cognitive behavioural therapy (CBT) which seek to modify behaviour, beliefs and coping strategies. [17-20]. Current best practice for the physical training of CFS patients involves GE sessions where the patient exercises at a well-tolerated constant rate or load (steady state), and the duration of the exercise session is gradually increased over time [2,18-20]. CBT is usually combined with exercise management [18,20].

Evidence of the efficacy of GE, CBT, pacing and other prescriptions of physical activity has been mixed. Some CFS patients still report symptom exacerbation and muscle pain with GE, and consequently are less likely to be physically active [21,22]. Yet other studies have reported that aerobic and resistance exercise improves aerobic capacity and strength [13], fatigue [17], profile of mood states and inflammatory cytokines [14,17,21,23-26].

Intermittent training, where intervals of exercise are alternated with intervals of rest or very low intensity exercise, has been used with cardiac [27], pulmonary [28,29], cancer [30] and older clients who are very deconditioned [31]. Clapp et al. (1999) reported that an acute session of intermittent exercise for 30 minutes did not exacerbate CFS symptoms immediately post-exercise, or for up to 7 days post exercise [32]. In CFS patients, intermittent training may increase exercise tolerance by decreasing perceived exertion, and delaying the onset of fatigue and muscle pain, whilst still providing the same total amount of physical activity as GE. Patients may find it easier to adhere to an intermittent exercise programme if their symptoms are not exacerbated, and therefore may improve their health.

Study hypotheses and aims: the primary aim of the trial is to investigate the efficacy of 12 weeks of intermittent or graded exercise on aerobic capacity, fatigue, immune function and wellness in CFS patients compared to standard care (typically rest, pharmacology and advice about physical activity). We hypothesise that:

1) Both exercise interventions will improve exercise tolerance, aerobic capacity and wellness compared to the control condition, and

2) IE will result in greater exercise tolerance, less fatigue and other symptoms, improved immune function and better exercise adherence compared to GE.

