### Participants

The inclusion criteria for the study are a medical diagnosis of CFS from the participant’s medical practitioner, according to CDC criteria; an age range of 16 to 60 yr; no diagnosed cardiorespiratory, endocrine, metabolic condition or current musculoskeletal injury that would make exercise participation hazardous; the ability to communicate in English; provision of informed consent; willingness to participate in three exercise sessions per week. Participants will be recruited from the local community through advertisements at the Southern Cross University campus and Health Clinic, local medical clinics and hospitals, local newspapers, television and radio media. Participants will be randomized *via* computer-generated randomly permuted blocks stratified by gender and age (< 40 years; > 40 years) into the intervention groups and control group. A university employee not involved in exercise testing or delivery of the intervention will prepare the randomization assignments. Group assignment will be delivered to participants in sealed envelopes upon the completion of baseline testing. Participants who have been randomized into the control group will be offered a supervised 12-week exercise program upon completion of the study.

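### The 82% power comes from a cohort of about 16-year-olds described as age-matched to a trial of ages 16 to 60, and it is not shown to be the power of the Bonferroni-adjusted contrasts with control that hypothesis 1 needs

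*Protocol article*

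**What the plan says.** **Planning data.** The section Sample size and power calculation takes VO2peak "data from a CFS sedentary, age-matched cohort (16.2±1.3 yr") from an earlier exercise study and says these data were used to compute power in G*Power.

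**Population.** The Participants section sets "an age range of 16 to 60 yr" and randomises in blocks "stratified by gender and age (< 40 years; > 40 years").

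**Power claim.** "Setting an alpha level of 0.05", "approximately 75 participants (25 per group) will provide 82% power to detect a statistically significant difference between groups". Recruitment is raised to 90 to allow for attrition. The assumed pattern is that "The control group is expected to experience no change in the aerobic capacity after 12-weeks while the intervention groups are expected to increase this measure".

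**Hypotheses (end of Background).** Hypothesis 1 says that both exercise programmes will improve exercise tolerance, aerobic capacity and wellness relative to control. Hypothesis 2 says that "IE will result in greater exercise tolerance, less fatigue and other symptoms, improved immune function and better exercise adherence compared to GE".

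**Analysis.** The Statistical analyses section plans repeated measures ANOVA with a Bonferroni adjustment between groups. It does not state how many comparisons the adjustment covers.

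**The concern.** There are two separate problems with one figure.

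First, the description of the source cohort conflicts with the trial's own eligibility rule. The word age-matched tells the reader that the planning effect and variability suit this trial. They were observed in a narrow adolescent group, while the trial expects enough patients over 40 to stratify on it.

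Second, the 82% is attached to an undefined difference between groups at an unadjusted 0.05. The aerobic capacity claim in hypothesis 1 is that each of two arms beats control, and the between-group comparisons are to be Bonferroni-adjusted. A reader will take 82% as the chance of confirming that hypothesis, and on the natural readings of the figure it is lower.

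What is at stake is how the trial is judged. If only one exercise arm, or neither, separates from control, the result will be read against a power figure that does not belong to those contrasts or, demonstrably, to that age range.

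**Working it through.** **1. Age.** Source cohort: mean 16.2, SD 1.3 years.
- Mean ± 2 SD = 16.2 ± 2.6 = 13.6 to 18.8 years, against 16 to 60 in the trial.
- If ages are roughly normal, the share below this trial's lower limit is Φ((16 − 16.2)/1.3) = Φ(−0.15) ≈ 0.44.

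The overlap with the eligible range is only its first few years.

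**2. Can 82% be reproduced?** Not directly. The article gives no effect size, SD, pre-post correlation, sidedness or test family. An article may leave these to the full protocol, so the check solves backwards from 82%, 25 per group and alpha 0.05.

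- *Omnibus F test, three groups, N = 75.* Noncentrality λ = N f², with 2 and 72 degrees of freedom. Power is 82% at f = 0.375 (λ = 75 × 0.375² = 10.55). For the protocol's pattern, control 0 and both exercise arms d, f = d√2/3, so d = 0.375 × 3/√2 = 0.80.
- *Two-sided two-sample t test.* Noncentrality d√(25/2), 48 degrees of freedom. Power is 82% at d = 0.83.
- *Group-by-time interaction, two time points.* In the G*Power form λ = f² × N × 2/(1 − ρ). At an assumed ρ = 0.5, 82% needs f = 0.1875, and λ = 0.1875² × 75 × 2/0.5 = 10.55. This equals the omnibus value, so the first line also covers this test, with d in units of the SD of change.

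**3. Power of each adjusted contrast with control.** Assumption: Bonferroni over three pairs, alpha = 0.05/3 = 0.0167 two-sided, critical t (48 df) = 2.48.

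| Reading of 82% | d | d√12.5 | Power per contrast |
|---|---|---|---|
| Omnibus or interaction | 0.80 | 2.81 | 63% |
| Pairwise t test | 0.83 | 2.93 | 67% |

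If the family were only the two contrasts with control (alpha 0.025), the figures would be 69% and 73%.

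**4. Power that both arms beat control.** The two contrasts share the control arm, so they are correlated. Simulation of three arms of 25 used pooled error (72 df) and alpha 0.05/3:

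| d | Both arms beat control | At least one does |
|---|---|---|
| 0.80 | 49% | 79% |
| 0.83 | 54% | 83% |

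Pooling the error moves the single-contrast power only slightly, to 64% and 69%.

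**5. Detectable difference.** Solving for 82% power with 25 per arm, alpha 0.05/3 and 48 df gives d ≈ 0.97 SD. This compares with the 0.80 to 0.83 SD implied by the stated 82%.

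**6. Intermittent versus graded exercise.** The power assumptions set control flat and both exercise arms rising. No difference between the two exercise arms is assumed, so the 82% does not apply to that comparison.

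**The case against.** **An alpha of 0.05 may be right for the test that was powered.** The wording fits an omnibus or group-by-time test, for which 0.05 is valid. The three-pair family is an inference, and power for at least one exercise arm to beat control stays at 79-83%, close to the stated figure. All of this stands. It does not supply the power of each named contrast, or of both together, and hypothesis 1 is worded for both.

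**A reader might infer that the wider age range cuts power by a definite amount.** The documents do not support that. VO2peak is analysed from pre and post values, and stable between-person spread cancels in change. Illustration with assumed values: SD 1 and correlation 0.80 give a change variance of 2(1 − 0.80) = 0.40, SD 0.632. Add stable between-person variance of 1.25, so that the SD is 1.5: the covariance is 0.80 + 1.25 = 2.05, the correlation is 2.05/2.25 = 0.911, and the change variance is 2(2.25 − 2.05) = 0.40, unchanged. Power falls only if the SD of change rises or the mean response is smaller in adults, and neither is shown.

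**A reader might infer that hypothesis 2 is an underpowered VO2peak hypothesis, or that a null result between the exercise arms will be taken as equivalence.** Hypothesis 2 does not name VO2peak, and the primary aim is comparison with standard care. Leaving a further hypothesis unpowered is ordinary in a trial whose abstract calls it a pilot. The analysis section already plans confidence intervals for group differences and labels an effect unclear when its interval spans substantial change in both directions. What remains is only that the scope of the 82% should be stated.

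**Age-matched may be carried over from matching inside the cited study.** Possibly. As written, it presents the cohort as matching this trial.

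**Conclusion.** The concern holds in two parts.

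The age-matched description is wrong on the page and needs no assumption to show it: 16.2 ± 1.3 years against 16 to 60 with a stratum above 40. Its effect on power cannot be sized from the documents. The 82% is uncertain for adults, not shown to be too high by a given amount.

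The 82% is also not shown to be the power of the contrasts that decide hypothesis 1. If it is an omnibus, interaction or single two-sided pairwise figure, and Bonferroni covers three pairs, power is about 63-67% for each exercise arm against control and about 49-54% for both. These figures take the back-solved effect of 0.80 to 0.83 SD as true and equal in both exercise arms. They show what the stated 82% implies and do not correct any stated input.

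**What to change.** In the sample size section:

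1. Delete the age-matched description.
2. Recompute power with VO2peak change data, including the SD of change, suited to ages 16 to 60. If no such data exist, say that the planning data are adolescent and that the power is uncertain for adults.
3. Name the test behind the power figure and the Bonferroni family. Keeping the same 75 evaluable and 90 recruited participants, restate the power, or the detectable difference, for each adjusted contrast (about 0.97 SD at 82% power with 25 per arm and alpha 0.05/3).
4. Say that the VO2peak calculation does not cover intermittent versus graded exercise, and that this comparison will be reported as an estimate with its interval.

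The cost is rewriting one paragraph and accepting a less favourable stated power. No participants, visits or measurements are added.

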**Methods/design:**

90 patients aged between 16 to 60 years, who meet the diagnostic criteria for CFS and have been diagnosed by their medical practitioner, will be randomly recruited into groups consisting of Intermittent exercise, Graded exercise and usual care (Control). The outcomes will be measured pre-study (Week 0) and post-study (Week 13). Primary outcomes are VO_2peak_, anaerobic threshold, peak power, levels of fatigue, immune cell (CD3^+^CD4^+^, CD3^+^CD8^+^, CD19^+^, CD 16^+^CD56^+^) concentrations and activation. Secondary outcomes include onset of secondary CFS symptoms (e.g. fever, swollen lymph nodes), wellness, mood and sleep patterns. Primary analysis will be based on intention to treat using logistic regression models to compare treatments. Quantitative data will be analysed using repeated measures ANOVA with a linear model, and Cohen’s effect size. Qualitative data such as participants’ responses (e.g. changes in mood and other reactions) following the exercise modalities will be read and sections demarcated. A code will be applied to each segment. A prevalence of codes will be considered thematically.

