### Statistical analyses

Primary analysis will be via intention-to-treat with all patients included regardless of dropout or level of adherence. Missing data will be imputed according to the maximum likelihood expectation algorithm via the Statistical Package for the Social Sciences (SPSS© Version 19.0). Physiological and exercise test data will be presented as the mean ± standard deviation, with confidence intervals used to express group differences. Changes between groups and the time effect for each group will be determined by repeated measures analysis of variance with a Bonferroni adjustment for significant differences between groups. Cohen’s Effect sizes and 90% confidence intervals will be calculated, to utilise a magnitude-based approach to inferences [41], with the following descriptors applied: (1) Effect size thresholds: <0.2 trivial, <0.6 small, <1.2 moderate, <2.0 large, <4.0 very large, >4.0 extremely large, and (2) Thresholds for assigning qualitative terms to chances of substantial effects: <0.5%, almost certainly not; <5.0%, very unlikely; <25%, unlikely; <75%, possible; >75%, likely; >95%, very likely; >99.5%, almost certain. An effect is unclear if its confidence interval includes both substantial increases and decreases [41]. A p value of < 0.05 will be considered indicative of statistical significance; clinical significance will be interpreted in light of the meaningfulness and magnitude of the adaptations observed. Data from linear pain scales will be recorded pre- and post-study, and reported as frequencies of scores between 0 and 10. Data will then be analysed using ANOVA (group and time effects). Data from wellness indices will be recorded pre and post, combined into domains and a representative total score from the time points analysed using an ANOVA. Data (non parametric) from the Fatigue scales, also measured at time points, will be collated and analysed using a Kruskall-Wallis test.

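### Recruiting 90 does not cover 20% attrition: a 20% loss leaves 72 participants, not the 75 on which the 82% power rests

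*Protocol article*

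**What the plan says.** The section Sample size and power calculation of the protocol article sets alpha at 0.05 and states that "approximately 75 participants (25 per group) will provide 82% power to detect a statistically significant difference between groups". The next sentence gives the recruitment target: "Recruitment will be inflated to 90 participants to enable a 20% participant attrition rate". The abstract repeats the target of 90 under Methods/design. No other attrition rate or inflation rule appears in the article.

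Under Statistical analyses the article adds: "Primary analysis will be via intention-to-treat with all patients included regardless of dropout or level of adherence". Missing values are to be imputed.

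No effect size, standard deviation, sidedness or G*Power test is given for the power calculation.

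**The concern.** The two adjacent sentences give a required number (75), an attrition rate (20%) and a recruitment target (90). Any two of these fix the third, and the printed set is not consistent. The number 90 is what results from adding 20% of 75 to 75. The allowance has to be taken from those recruited, and 20% of 90 is 18, more than the 15 extra participants provided.

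The sentence assures readers and the ethics committee that the trial can lose one participant in five and keep its stated power. Anyone tracking retention against it would treat up to 18 losses as planned for, when the real margin is 15. The allowance may well be used: the programme runs for 12 weeks at three supervised sessions a week, and the Background notes that some patients report worse symptoms with graded exercise.

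**Working it through.** **Inputs, all from the section Sample size and power calculation**

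- Required number: about 75, in three equal groups of 25
- Power at that number: 82%, with alpha 0.05
- Attrition: 20%
- Recruitment target: 90 (also in the abstract)

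**Step 1. Reproduce the plan's figure.** Multiplying the required number by one plus the attrition rate gives 75 × (1 + 0.20) = 90. This matches exactly.

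**Step 2. Apply the correct inflation.** If a fraction d of those recruited is lost, recruiting N leaves N × (1 − d). Setting this equal to n gives N = n/(1 − d).

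- In total: 75/(1 − 0.20) = 93.75, so 94.
- Per group: 25/0.80 = 31.25, so 32, and 3 × 32 = 96 with equal groups.

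**Step 3. Work forward from 90.**

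- Left after 20% loss: 90 × 0.80 = 72, or 24 per group. This is 3 short of 75.
- Largest loss that still leaves 75: (90 − 75)/90 = 15/90 = 16.7%.

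**Step 4. Gauge the effect on power.** The protocol's effect size is not given, so this step rests on an assumption. For each plausible test, I solved for the standardised effect that gives 82% power at 25 per group, then recomputed power at 24 per group with that effect.

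| Test assumed | Effect giving 82% at 25 per group | Power at 24 per group |
|---|---|---|
| Three-group F test, alpha 0.05 | f = 0.375 | 80.2% |
| Pairwise t test, two-sided 0.05 | d = 0.83 | 80.4% |
| Pairwise t test, one-sided 0.05 | d = 0.73 | 80.6% |
| Pairwise t test, two-sided, Bonferroni for three comparisons (0.05/3) | d = 0.97 | 80.1% |

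For the F test the noncentrality is f² × N, with 2 and N − 3 degrees of freedom. It is 0.375² × 75 = 10.55 at N = 75 and 0.375² × 72 = 10.13 at N = 72. For the t tests the noncentrality is d × √(n/2), with 2n − 2 degrees of freedom. In the two-sided case it is 0.83 × √12.5 = 2.93 at n = 25 and 0.83 × √12 = 2.88 at n = 24.

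A repeated-measures version of the F test (group-by-time interaction, two time points, assumed correlation 0.5), solved in the same way, also gives 80.2%. The loss across all these tests is about 1.4 to 1.9 percentage points.

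**The case against.** The strongest reply is that the gap is trivial. The protocol says *approximately* 75, 72 is within 4% of that, the abstract calls the study a pilot, and implied power stays at or just above 80%. This stands as a statement about size: nothing in the randomisation or analysis changes. It does not reconcile the figures. The 82% is tied to 25 per group, a 20% loss leaves 24, and the exact match of 90 with 75 × 1.20 points to a formula slip more than to rounding. The article does not state how 90 was obtained, so that cause is an inference, though the mismatch does not depend on it.

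A second reply is that intention-to-treat with imputation keeps all 90 in the analysis. Imputation keeps dropouts in the analysis set but does not restore the information in their missing Week 13 measurements. The sample size section itself treats attrition as a loss that needs extra recruits.

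A third reply is that the power at 72 cannot be known, because the effect size, standard deviation and test are not stated. It is true that the 82% cannot be rebuilt from the document, and nothing here disputes it. But moving from 25 to 24 per group with the effect held fixed gives almost the same answer for every test tried, so describing the result as about 80% on the same assumptions is safe. The sponsor can confirm it from the original G*Power inputs.

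**Conclusion.** The attrition statement is wrong as written. Recruiting 90 allows 16.7% attrition if 75 are to remain. At the stated 20%, 72 remain (24 per group), and keeping 75 would need 94 recruits, or 96 in equal groups. These figures follow from the protocol's own numbers and need no assumption beyond reading attrition as a share of those recruited.

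The consequence is small: 3 participants in total and a fall in power from 82% to about 80% (80.1% to 80.6%). That power range takes the stated 82% at 25 per group as correct and holds the implied effect fixed. The finding does not show that 75 is the wrong number or that the trial is inadequately sized. It warrants a correction of the text, not a change of design.

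**What to change.** Keep 90 and replace the recruitment sentence with wording such as: *Ninety participants will be recruited, which allows for 16.7% attrition while retaining 75; at 20% attrition 72 (24 per group) would remain, giving about 80% power on the same assumptions.* The sponsor should confirm the last figure from the original G*Power inputs. The cost is one sentence and a slightly less favourable stated allowance, with no extra patients.

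If the sponsor prefers to keep both 82% power and the 20% allowance, the target should rise to 94, or 96 with equal groups. That means 4 to 6 more participants and a matching change to the number in the abstract.

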### Participants

The inclusion criteria for the study are a medical diagnosis of CFS from the participant’s medical practitioner, according to CDC criteria; an age range of 16 to 60 yr; no diagnosed cardiorespiratory, endocrine, metabolic condition or current musculoskeletal injury that would make exercise participation hazardous; the ability to communicate in English; provision of informed consent; willingness to participate in three exercise sessions per week. Participants will be recruited from the local community through advertisements at the Southern Cross University campus and Health Clinic, local medical clinics and hospitals, local newspapers, television and radio media. Participants will be randomized *via* computer-generated randomly permuted blocks stratified by gender and age (< 40 years; > 40 years) into the intervention groups and control group. A university employee not involved in exercise testing or delivery of the intervention will prepare the randomization assignments. Group assignment will be delivered to participants in sealed envelopes upon the completion of baseline testing. Participants who have been randomized into the control group will be offered a supervised 12-week exercise program upon completion of the study.

